
### 2.9. Study Endpoints

Primary composite endpoint (score 0–6):

The primary composite endpoint was designed to capture procedural efficiency and safety rather than long-term clinical outcomes. Individual components were selected to reflect aspects of PCI that may be directly influenced by improved preprocedural anatomical understanding and planning, including resource utilization, procedural complexity, and periprocedural myocardial injury. The composite score is intended as a pragmatic measure of procedural optimization rather than a surrogate for clinical outcome.

Need for intravascular imaging (IVUS).Occurrence of major procedural complications (perforation, severe dissection, stent malapposition, or under-expansion requiring post-dilatation, main/side branch occlusion).Post-procedural high-sensitivity troponin T elevation >5-fold compared to baseline at 24 h.Contrast volume > 200 mL as established in prior interventional studies.Radiation dose > predefined threshold (estimated effective dose of >16.1 mSv) according to institutional and published reference levels for PCI procedures [14].

Hospital stay > 2 days. Secondary endpoints (exploratory):

In-hospital MACE and complications or the need for repeated cardiac catheterization with or without reintervention during the index hospitalization or within 30 days after the procedure.

Long-term major adverse cardiac events (MACE): cardiac death, probable or definitive stent thrombosis, non-fatal myocardial infarction, or target-lesion revascularization at 12 and 24 months.

Guiding catheter changes or unplanned use of lesion preparation techniques.

Procedural efficiency metrics (procedure duration, fluoroscopy time, material consumption, and cost-effectiveness).

Patient-reported outcomes: quality of life using the SAQ-7 questionnaire.

Clinical events and complications are defined according to established consensus criteria, including Academic Research Consortium (ARC) definitions for stent thrombosis and target-lesion failure and Society for Cardiovascular Angiography and Interventions (SCAI) criteria for procedural complications. Imaging-derived findings are reported separately and are not classified as clinical events unless they meet these standardized definitions.

Figure 1 summarizes the methodological aspects and flowchart of the trial.

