The aim of PRECISION-CT is to determine whether CCTA-guided PCI planning improves procedural strategy and execution in patients undergoing non-emergent revascularization. By integrating pre-PCI CCTA findings with procedural characteristics and clinical outcomes, the trial aims to clarify how CT-based planning can refine interventional strategies, reduce procedural uncertainty and reduce the need for intravascular imaging, thus optimizing resource utilization, procedural time, costs, patient safety, contrast volume, and radiation exposure. All these aspects may thereby ultimately introduce a more personalized and evidence-based approach to PCI. Figure 1 summarizes the methodological aspects and flowchart of the trial. 

Importantly, the PRECISION-CT study evaluates the incremental value of structured, quantitative, and real-time CCTA integration into the catheterization laboratory compared with standard-of-care CCTA-informed PCI. This design reflects contemporary clinical practice, where CCTA is frequently available prior to ICA, and focuses on whether enhanced integration of existing imaging data can improve procedural planning, efficiency, and safety.

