### 2.6. Randomization and Study Arms

Randomization will be performed after completion of CCTA analysis and prior to invasive coronary angiography. Participants will be randomized (1:1) into two groups using sequentially numbered, opaque, sealed envelopes. The randomization sequence will be generated by an independent study nurse. Sequentially numbered, opaque, sealed envelopes will be prepared centrally and stored securely. After written informed consent and patient inclusion, the envelope will be opened immediately before PCI by a study nurse not involved in outcome assessment. Operator blinding is not feasible due to the nature of our study. For patients allocated to the intervention arm, anonymized CT datasets will be transferred securely to the image-analysis site in Switzerland (Nuclear Medicine Department) using the USZ Secure Transfer Platform (https://transfer.usz.ch/). There, detailed CT analysis and three-dimensional reconstructions will be performed using CE-marked post-processing software (GE Healthcare Advantage Workstation, AW, Version 4.7). CT data transfer requires approximately 10 min, and structured image analysis and procedural planning require approximately 30 min, ensuring cost- and time-effectiveness. Only elective PCI cases will be included, which undergo ambulatory CCTA and are then scheduled for elective PCI based on CCTA and clinical data, or if required additional stress test preprocedural findings; therefore, CT processing will not delay urgent or emergent care. The analysis results will be returned to the German study site prior to PCI and made available during the procedure. Treating operators will be informed of group allocation immediately before the PCI procedure to minimize allocation-related scheduling or case-selection bias. Participating operators have >5 years of experience in interventional cardiology and are board-certified with a formal focus in Interventional Cardiology of the German Cardiac Society (DGK).

**Intervention arm**: Full CCTA analysis, including 3D reconstructions, is displayed on an integrated monitor (3D Tabcard, CPQ-1511578) in the catheterization laboratory during PCI and can directly guide procedural decisions.

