### 2.7. PCI Procedure and CT-Guided Planning

Interventional cardiologists will receive a standardized CCTA report prior to the PCI procedure during the pilot study phase for all patients and during the randomized study for the patients randomized to the CCTA-guided PCI arm. The report contains annotated images and textual descriptions covering optimal angiographic projections, reference vessel diameters, lesion length, calcium distribution, and bifurcation anatomy to guide stent and device selection. A representative file report is provided in the Supplementary Materials, illustrating how quantitative and actionable information is communicated consistently to the operator. Procedural planning includes:•Maximal Intensity Projection (MIP) images of the coronary tree.•Exact location and height of coronary ostia.•Axial images of coronary arteries.•Multiplanar reformation (MPR) images of coronary arteries.•Short-axis cross-sectional images.•Lesion length.•Bifurcation anatomy and vessel tortuosity, as well as a suggested provisional stenting versus a two-stent approach.•Calcification burden, including the arc of the calcification in degrees and the calcification length.•Lesion morphology, including the presence and extent of mixed and non-calcified plaques.•Optimal C-arm angulation angles.•The need for lesion preparation (rotational atherectomy or intravascular lithotripsy), choice of guiding catheter, stenting strategy, and projection angles may be adapted accordingly.

Intravascular imaging will not be discouraged in either study arm and will be encouraged in both arms in certain clinical scenarios and based on current guideline recommendations. Thus, operators may perform IVI based on pre-specified bail-out criteria, including uncertain lesion length or morphology, suboptimal stent expansion or malapposition, complex bifurcation anatomy, heavy calcification, or any safety concern. All IVI use, including specific indications for imaging, will be prospectively documented. Notably, the “need for IVI” in the composite endpoint reflects procedural escalation and resource utilization and not an adverse clinical event.

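### The primary score gives a point for IVUS use, which an unblinded operator decides and the intervention aims to reduce, so a lower score alone cannot support a safety conclusion

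*Protocol article*

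**What the plan says.** Section 2.9 of the Protocol article defines the "Primary composite endpoint (score 0–6") with six items and gives no weights. Two items matter here:

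- Item 1: "Need for intravascular imaging (IVUS").
- Item 2: "Occurrence of major procedural complications (perforation, severe dissection, stent malapposition, or under-expansion requiring post-dilatation, main/side branch occlusion").

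Section 2.9 closes with a rule: "Imaging-derived findings are reported separately and are not classified as clinical events unless they meet these standardized definitions".

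Section 2.7 leaves imaging to the operator: "operators may perform IVI based on pre-specified bail-out criteria, including uncertain lesion length or morphology, suboptimal stent expansion or malapposition, complex bifurcation anatomy", with heavy calcification and any safety concern also listed. It adds that IVI is not discouraged in either arm, that each use and its indication is documented, and that the IVI item "reflects procedural escalation and resource utilization and not an adverse clinical event".

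Section 2.6 states: "Operator blinding is not feasible due to the nature of our study". The Introduction says the trial should show how CT-based planning can "reduce procedural uncertainty and reduce the need for intravascular imaging". The Abstract describes the composite as a score of procedural safety and efficacy, and section 2.9 says it captures efficiency and safety.

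**The concern.** Item 1 is a choice, made by someone who knows the arm, about something the intervention is meant to reduce. Every patient who is not imaged scores one point less, whether or not anything else about the procedure improved. Because the items are unweighted, one IVUS run counts as much as a perforation.

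The plan itself says this item is resource use and not harm, yet it feeds a score described in terms of safety. The trial could report a better safety and efficacy score when imaging use was the only thing that changed.

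Item 2 raises a lesser question. Malapposition and under-expansion are findings that IVI may reveal more readily, so an arm that images less may also record fewer of them.

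**Working it through.** **1. The plan's own figure.** Section 2.11 assumes 50% against 30%, 100 per arm, two-sided α of 0.05, and claims more than 80% power.

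z = (|p1 − p2|·√n − 1.96·√(2·p̄·(1 − p̄))) / √(p1(1 − p1) + p2(1 − p2))
= (0.20 × 10 − 1.96 × √(2 × 0.4 × 0.6)) / √(0.25 + 0.21)
= (2 − 1.358) / 0.678 = 0.947, which gives a power of 82.8%.

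The figure reproduces. The point concerns what the endpoint measures, not the sample size.

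**2. Effect of item 1 on the mean score.** The mean of an unweighted score is the sum of the item probabilities. If the other five items are equal between arms, the difference in means equals the difference in IVI use. The documents give no IVI rates, so these are assumptions. For 40% against 20%, with the other five items at 5% each: 0.40 + 5 × 0.05 = 0.65 against 0.20 + 5 × 0.05 = 0.45, a difference of 0.20.

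**3. How often that alone is significant.** Simulated trials with 100 per arm, independent items and no difference in any item except IVI use, tested by Mann–Whitney on the 0–6 score. Ranges cover repeated runs of 2,000 to 5,000 trials.

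| IVI use, control vs CCTA-guided | Other five items 5% each | Other five items 10% each |
|---|---|---|
| 40% vs 20% | 60–63% | 43–45% |
| 40% vs 15% | 79–80% | 59–63% |
| 50% vs 20% | 91–93% | 76–77% |
| IVUS point removed | about 5% | about 4–5% |

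The article does not say how the score is to be tested. A chi-square test on a score of at least 1 gives similar results. In the row order of the table these are 63%, 81% and 94% with the others at 5%, and 42%, 58% and 74% with the others at 10%.

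On that second reading, the probability of any point is 1 − (1 − p_IVI)(1 − q)^5. With q = 5%, (0.95)^5 = 0.774. IVI use of 40% against 15% then gives 1 − 0.60 × 0.774 = 53.6% against 1 − 0.85 × 0.774 = 34.2%. That 19-point gap is almost the whole 20-point effect the trial is designed to detect, from imaging use alone.

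**4. Detection through item 2.** Assume malapposition or under-expansion is found in 90% of cases with IVI and 30% without (not in the documents). Recorded rate = true rate × (IVI × 0.9 + (1 − IVI) × 0.3).

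- True rate 20%, IVI 40% vs 20%: 0.20 × 0.54 = 10.8% vs 0.20 × 0.42 = 8.4%. Difference 0.024 points, against 0.20 from item 1.
- True rate 30%, IVI 60% vs 30%: 0.30 × 0.66 = 19.8% vs 0.30 × 0.48 = 14.4%. Difference 0.054 points, against 0.30 from item 1.

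With 20% detection without IVI and true rates of 10% to 30%, the difference is 0.014 to 0.063 points. If an event means a score of at least 1, detection adds nothing while item 1 is in the score, because every imaged patient already has a point. With the IVUS point removed and item 2 unchanged, that reading is significant in about 3% to 12% of trials.

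**5. Item 2 beside the imaging rule.** Item 2 lists malapposition, and under-expansion needing post-dilatation, among major complications without condition. The closing rule of section 2.9 keeps imaging-derived findings apart from clinical events unless they meet the cited standard definitions. A reader cannot tell whether a malapposition seen only on IVUS scores. The article does not require the stent result to be judged in the same way in both arms.

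**The case against.** The plan is open about item 1. It calls it resource use, does not discourage IVI in either arm, sets bail-out criteria, records every use with its indication, and names performance bias as a limitation in the Discussion. Section 2.9 describes the score as a pragmatic measure of procedural optimization, not a surrogate for clinical outcome. Less IVI is a declared goal, so the percentages above are not false-positive rates: they show a declared component moving the endpoint. This stands, and it is why item 1 may stay in the score. It does not reach the safety wording, since documenting an indication does not change what is scored.

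The inputs are also assumed. The 50% IVI scenarios imply control rates of any point of 1 − 0.50 × 0.774 = 61% and 1 − 0.50 × 0.590 = 70%, where (0.90)^5 = 0.590. Both exceed the 50% in section 2.11. The 40% scenario with the others at 5% gives 54%, close to it, and the conclusion is unchanged there.

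A reader might infer more: that two of the six points hinge on imaging, that malapposition is mostly visible only with imaging, and that less imaging is rewarded twice. The documents do not support this. Perforation, severe dissection and branch occlusion do not rest on IVI. Section 2.7 lists suspected malapposition or poor expansion as a reason to start IVI, so it can be suspected beforehand. For under-expansion, item 2 requires that post-dilatation was needed. The second reward is small by the arithmetic above. Nor does section 2.9 already require these findings to be deleted from the score, because its rule has an exception for findings that meet the standard definitions. Stent problems that went unseen could also surface in the 30-day and the 12- and 24-month secondary endpoints.

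**Conclusion.** The concern holds for item 1 and should be fixed. A fall in IVI use of 20 to 30 percentage points, with nothing else different, makes the primary score significantly lower in about 44% to 93% of trials, against about 5% without the IVUS point. This rests on assumed IVI rates, other items at 5% to 10% each, independent items, and a test that the article does not specify. The direction does not depend on these assumptions: the score falls by the drop in IVI use. A lower total is therefore evidence of less imaging, of better procedures, or of both, and cannot alone carry a safety claim.

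Item 2 is secondary. Its wording and the imaging rule of the same section need to be reconciled, but the likely detection effect is only about 0.02 to 0.05 points under the 90% and 30% detection rates assumed.

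**What to change.** - Keep the primary score. Pre-specify the score without the IVUS point as the key supportive analysis, and state that any safety conclusion rests on it.
- Report IVI use as a resource outcome, and show every item by arm.
- Reconcile item 2 with the imaging-findings rule in section 2.9. Either report malapposition and under-expansion separately from the score, or count them only on a criterion that does not depend on IVI having been used and is applied identically in both arms.

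The cost is wording plus one extra analysis. Item 2 may become slightly rarer, which lowers the overall event rate a little. The change should be made before results by arm are seen.

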**Control arm**: The operator reviews the standard clinical CCTA report and images prior to ICA/PCI according to institutional standard operating procedures, without structured quantitative post-processing, procedural planning recommendations, or real-time visualization in the catheterization laboratory.

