### 2.8. Data Collection

Data will be collected prospectively and will be entered into a standardized database. The collected variables include:▪**Demographics**: age, gender, date of admission, and length of hospitalization.▪**Indications for CCTA and ICA**: typical angina pectoris, atypical angina pectoris, non-anginal chest pain, or presence of dyspnea.▪**Medical history and cardiovascular risk factors**: prior myocardial infarction, hypertension, dyslipidemia, diabetes mellitus, current or prior cigarette smoking, chronic obstructive pulmonary disease, chronic kidney disease, atrial fibrillation, or peripheral artery disease.▪**Cardiac medications at baseline.**▪**Echocardiographic data**: left ventricular ejection fraction (LVEF) or presence of regional wall motion abnormalities.▪**CCTA data:**oAnatomic lesion location, including segment number and classification into proximal, mid, or distal vessel.oOstial involvement and measurement of coronary ostium height from the aortic annulus.oTakeoff angle of right and left coronary ostia, assessed using clock-face reference.oPlaque composition (calcified, non-calcified or mixed based on the presence of the calcified content by visual criteria of >80%, 20–80% and <20% calcium content) [12].oPresence of high-risk plaque features, including: positive remodeling, napkin-ring sign, low attenuation plaque (<30 HU) or spotty calcification [13].oTotal coronary calcium score quantified using the Agatston score.▪**Invasive procedural data**: Comprehensive data from invasive coronary procedures will be collected, including: use of advanced intracoronary imaging (IVUS if necessary), use of physiological assessment (FFR or iFR/RFR if necessary), number of stents implanted, their total length, stent diameters, the use of re-dilation, including the use of scoring balloons and the corresponding pressures, and the use of lesion modification techniques (rotablation or/and intravascular lithotripsy), and bifurcation stenting strategies including provisional versus bifurcation stenting if necessary.▪**Procedural outcomes and metrics**: Final TIMI flow grade, residual stenosis in percentage, procedural success, defined as final TIMI 3 flow with <20% residual stenosis in the treated segment and absence of in-hospital major adverse procedural events, additional procedural metrics included total fluoroscopy time (minutes), radiation exposure (mGy), contrast volume used (ml), and total procedure duration (minutes).▪**Operator feedback and satisfaction:**oUse of CT-based projections during PCI.oPrediction of stent dimensions (length and diameter) based on CCTA measurements.oPrediction of landing zones for stent deployment.oSatisfaction with CCTA planning (1–5 scale for both primary and secondary operators).oPerceived benefit of CCTA-derived data on ostial angle, lesion length, plaque quality and projection guidance, helping with reducing procedure time, fluoroscopy exposure and complications.oWhether CCTA planning helped in avoiding unnecessary PCI or reducing the number of stents required for lesion treatment.

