### 2.11. Statistical Analysis

Descriptive statistics will be used to characterize the patient population, procedural details, and outcomes. Categorical variables will be reported as counts and percentages and compared using the chi-square or Fisher’s exact test. Continuous variables will be assessed for normality using the Shapiro–Wilk test. Variables that are normally distributed will be presented as mean ± standard deviation and compared using *t*-tests, while non-normally distributed variables will be presented as median (interquartile range) and compared using Mann–Whitney U tests. To assess the impact of CT planning on procedural outcomes, univariate and multivariable logistic regression models will be applied. Variables with a *p*-value < 0.10 in univariate analysis will be included in the multivariable models using a backward stepwise approach. Odds ratios (OR) with 95% confidence intervals (CI) will be reported. The primary analysis will be performed according to the intention-to-treat principle.

Procedural metrics (e.g., contrast volume, fluoroscopy time, radiation dose, procedure duration) will additionally be assessed using linear regression models. Receiver operating characteristic (ROC) curve analyses will be performed to evaluate the diagnostic performance of specific CT features (e.g., ostial angle, lesion length, plaque morphology) for predicting procedural complications or strategy changes. The area under the curve (AUC) with 95% CI will be calculated. Interobserver and intraobserver variability for CCTA-derived measurements (e.g., ostial height, takeoff angle, lesion length) will be assessed using intraclass correlation coefficients (ICC) for continuous variables and Cohen’s κ for categorical variables.

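### Unplanned lesion preparation, an exploratory secondary endpoint, is not measured alike in the two arms, so identical care can score differently, in either direction

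*Protocol article*

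**What the plan says.** Section 2.9 of the Protocol article places "Guiding catheter changes or unplanned use of lesion preparation techniques" among the secondary endpoints, which it labels exploratory. No reference for 'unplanned' is given.

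Section 2.7 says who receives the standardized CCTA report: all patients' operators in the pilot phase, but "during the randomized study for the patients randomized to the CCTA-guided PCI arm". Its list of planning content ends with "The need for lesion preparation (rotational atherectomy or intravascular lithotripsy), choice of guiding catheter, stenting strategy, and projection angles may be adapted accordingly".

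Section 2.6 describes the control arm in two parts. First, "The operator reviews the standard clinical CCTA report and images prior to ICA/PCI according to institutional standard operating procedures". Second, this happens "without structured quantitative post-processing, procedural planning recommendations, or real-time visualization in the catheterization laboratory".

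Section 2.8 lists "the use of lesion modification techniques (rotablation or/and intravascular lithotripsy" among the invasive procedural data. It lists no item for the strategy intended before PCI, in either arm. Section 2.6 also states that operators cannot be blinded and that they learn the allocation immediately before the procedure.

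**The concern.** Lesion preparation can be called unplanned only by comparison with a plan fixed beforehand. Here the trial's only written plan is part of the intervention. In the CCTA arm an assessor can look up whether atherectomy or lithotripsy was foreseen. In the control arm there is nothing to look up, so the classification falls to a convention that the article does not state, or to the later account of an operator who knows the allocation.

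The component could then show a difference between arms when device use and operator behaviour are the same. That matters because the Introduction names reducing procedural uncertainty as one of the trial's aims, and this endpoint speaks to it directly. The problem also cannot be repaired at analysis, because an intention not recorded before PCI cannot be recovered afterwards.

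**Working it through.** **The plan's own figure.** No rate or power is given for this endpoint. The only stated power is more than 80% for the primary endpoint (section 2.11: about 50%, 20-point absolute reduction, 100 per arm, two-sided 0.05). By the normal approximation, the standard error under the null is √(2 × 0.4 × 0.6/100) = 0.0693 and under the alternative √((0.25 + 0.21)/100) = 0.0678. Power is Φ((0.20 − 1.96 × 0.0693)/0.0678) = Φ(0.947) = 0.828, so the stated figure reproduces. It is not in question here.

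**Inputs for the illustration.**
- n = 100 per arm (section 2.11).
- L = 15%, true use of lesion preparation, the same in both arms. Assumed; the article gives no rate.
- s = 2/3, the share of that use foreseen in the CCTA report. Assumed.
- c = the share of control use accepted as planned. This depends on the missing convention, so it is varied.

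**Formula.** Counted rate in the CCTA arm = L(1 − s) = 0.15 × 1/3 = 5%. Counted rate in the control arm = L(1 − c). The chance of p<0.05 sums the binomial probabilities of all tables that reach significance. Section 2.11 names chi-square or Fisher's exact test, so both are shown (chi-square without continuity correction).

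| Convention for control use | Control v CCTA | Chi-square | Fisher |
|---|---|---|---|
| All counts as unplanned (c = 0) | 15% v 5% | 68% | 59% |
| Half accepted as planned (c = 1/2) | 7.5% v 5% | 11% | 7% |
| Both arms plan alike (c = 2/3) | 5% v 5% | 4% | 2% |
| Use without a written plan cannot be unplanned (c = 1) | 0% v 5% | 74%, reversed | 38%, reversed |

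The last row can be checked by hand. With no control events, chi-square reaches significance at 4 or more CCTA events (statistic 4.08), and P(X ≥ 4) for a binomial with n = 100 and rate 0.05 is 0.742. Fisher's test needs 6 or more (p = 0.029; with 5 events p = 0.059), and P(X ≥ 6) = 0.384.

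**Effect of the assumed rates.** With c held at 0, the chi-square chance is 27% for 10% use with half foreseen (10% v 5%), 82% for 20% use with two thirds foreseen (20% v 6.7%), and 96% for 30% use with two thirds foreseen (30% v 10%). These figures vary L and s only. The table shows that c matters more, since it alone moves the result from a clear apparent benefit to a clear apparent harm.

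**Effect of the other half of the endpoint.** If guiding catheter changes and unplanned preparation form one composite, and catheter changes occur independently in a fraction g of both arms (assumed), the rate is 1 − (1 − g)(1 − u), where u is the unplanned rate. For u = 15% v 5%, g = 10% gives 23.5% v 14.5% (37% chance of p<0.05 by chi-square) and g = 20% gives 32% v 24% (24%). The distortion is diluted but does not disappear.

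**The case against.** A reader might infer that the control arm scores worse by construction. The documents do not support that. Nothing says that control use defaults to unplanned. Control operators review the CCTA report and images, and the Discussion describes operators mentally simulating device strategies and lesion preparation within 24 hours of the procedure. Lacking trial-supplied recommendations is not the same as lacking a plan. If 'unplanned' means departure from a written plan, the bias runs against the CCTA arm. This objection stands, and the point is therefore made without a direction.

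A second tempting extension is to the ROC analyses in section 2.11, which use CT features "for predicting procedural complications or strategy changes". 'Strategy changes' also has no stated reference there, but that analysis is not a comparison between arms, so the arm-dependent distortion does not carry over.

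It can also be said that an article condenses the protocol and that one word may be defined elsewhere. A full protocol or case report form may indeed hold the definition. But the arms and the list of collected variables are set out here in detail, and taken together they leave the component without a common reference. Because this concerns what is recorded before PCI, an analysis plan alone could not settle it.

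Finally, the endpoint is exploratory, the limitations already concede performance bias from unblinded operators, and guiding catheter changes need no plan to be counted. All of this stands and limits the consequence.

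**Conclusion.** The lesion-preparation component is measured differently in the two arms, and a difference in it could not be interpreted. With 15% use in both arms and two thirds foreseen in the CCTA arm, identical care gives anything from 10 points in favour of CCTA guidance to 5 points against it, according to an unstated convention. The use rate and the share foreseen are assumptions, and the percentages describe this component alone. That the reference is supplied in one arm only follows from the text; the direction of any bias does not. Guiding catheter changes, the 0–6 primary score and the sample size are untouched. The change should be made before randomized cases accrue, but it does not threaten the main result.

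**What to change.** 1. In both arms, have the operator record the intended lesion preparation (yes/no, and type) on the same minimal form just before arterial access, after reviewing whatever CCTA material that arm allows.
2. Define 'unplanned' in section 2.9 as departure from that record, identically in both arms.
3. Report guiding catheter changes and unplanned lesion preparation separately.
4. Report total lesion-preparation use by arm beside them. It is already collected, and it shows whether care itself differed.

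The cost is a very short form, one to two minutes per case, and one sentence in the endpoint definition. No treatment rule and no sample size changes. There are two small downsides. The form slightly formalises control-arm practice, so it should record intention only and give no recommendations. It is also completed by an unblinded operator, who could list too much; planned preparation that was not used should be visible from the same form.
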